### Statistical methods

Clinical efficacy will be assessed as non-inferiority of Tr14 injection solution with respect to dexamethasone regarding the primary efficacy parameter. A one-sided test of non-inferiority of Tr14 injection solution with respect to dexamethasone at level 0.025 will be computed using an analysis of covariance (ANCOVA) model with treatment group and center as qualitative factors and the baseline value of the abduction rotation pain VAS for active external rotation as a covariate.

All continuous efficacy parameters will be analyzed by suitable analysis of ANCOVA models, whereas the dichotomous Jobe and painful arc test data will undergo suitable logistic regression model analyses. The ordered categorical responses of the patients’ and examiners’ global assessment will be evaluated by Cochran-Mantel-Haenszel (CMH) tests that account for stratification by center. Clinical safety will be addressed by assessing AEs, physical examinations, laboratory assessments, and vital signs results in a descriptive manner. All statistical analyses in this study will be exploratory in nature.

Analyses will be based on the safety analysis, full analysis, and the per-protocol sets. The summaries of the efficacy parameters, the statistical analyses of the primary efficacy variable, and the statistical analyses of the secondary efficacy variables will be performed on the per-protocol set. These summaries and analyses will be supported by corresponding summaries and exploratory statistical analyses performed on the full analysis set. Missing values for all efficacy parameters will be imputed by the last observation carried forward (LOCF) approach. All statistical tests will be supported by presenting estimates and 95% confidence intervals for the respective treatment effects and differences between the treatment groups. These estimates and confidence intervals will be based on the respective statistical models used for the analysis, shown in Table 3.

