### Sample size calculation

Estimation of sample size is based on the primary efficacy variable, change from baseline in abduction rotation pain VAS for active external rotation. A one-sided *t*-test of non-inferiority at level 0.025 based on a non-inferiority margin of 13 mm and a standard deviation of 25 mm for the response variables achieves a power of 80% computed for equal treatment effects if the sample size is set to 60 patients per active treatment group in the per protocol set. Assuming a dropout rate of 6.25%, at least 160 patients should be randomized (i.e. 64 patients per active treatment group and 32 in the placebo group).

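### Non-inferiority is decided on the per-protocol set alone; it should have to hold in the full analysis set as well

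*Protocol article*

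**What the plan says.** The primary test is "A one-sided test of non-inferiority of Tr14 injection solution with respect to dexamethasone at level 0.025", by analysis of covariance (Statistical methods). The same section assigns the analysis sets: "the statistical analyses of the primary efficacy variable, and the statistical analyses of the secondary efficacy variables will be performed on the per-protocol set". On the full analysis set it says: "These summaries and analyses will be supported by corresponding summaries and exploratory statistical analyses performed on the full analysis set". Nothing in the article requires the two sets to agree before non-inferiority is concluded. Missing efficacy values are filled by LOCF, and every analysis in the study is labelled exploratory.

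The section Sample size calculation follows the same choice. It requires "60 patients per active treatment group in the per protocol set" and continues: "Assuming a dropout rate of 6.25%, at least 160 patients should be randomized".

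Criteria for withdrawal of patient from study lists an inefficacy rule (pain VAS at least 30 mm above baseline at two consecutive visits) and the occurrence of a condition that requires prohibited medication, including NSAIDs and analgesics other than paracetamol. Table 2 puts the visits after baseline on days 8, 15 and 22, and day 22 is the primary time point.

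**The concern.** A per-protocol set is formed after randomization. Some of the events that can end a patient's participation here are themselves results of treatment: pain that rises, or pain that needs a stronger drug. If such patients leave the primary set and there are more of them on Tr14, the Tr14 patients who remain look more like the dexamethasone patients than the randomized groups do. In a non-inferiority trial that error favours the claim.

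Per-protocol analysis is customary in this setting for a good reason, since including deviators can also blur a real difference. Each set can therefore mislead in its own way, which is the argument for requiring both. As written, a per-protocol success stands even when the full analysis set fails.

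The Tr14 versus placebo comparisons in Table 3 are also placed on the per-protocol set. There too, exclusions after randomization weaken the protection that randomization gives.

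**Working it through.** **Inputs from the protocol article.** One-sided level 0.025 (Statistical methods); "non-inferiority margin of 13 mm and a standard deviation of 25 mm for the response variables"; a design that "achieves a power of 80% computed for equal treatment effects"; 60 per active arm in the per-protocol set and 64 randomized (Sample size calculation).

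**1. The plan's own figures.** With n per arm, noncentrality = 13 / (25 × √(2/n)) on 2n − 2 degrees of freedom.
- n = 59: noncentrality 2.824, power 79.98%.
- n = 60: noncentrality 2.848, power 80.6%.
- 60 / (1 − 0.0625) = 64 per active arm, and 64 + 64 + 32 = 160.

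The stated 60, 64 and 160 all reproduce.

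**2. Can outcome-related withdrawal precede the endpoint?** The inefficacy rule needs two consecutive visits. Days 8 and 15 can meet it before day 22. If days 15 and 22 meet it, the primary value has already been observed. Withdrawal for prohibited medication is not tied to a visit and can happen on any day. So the answer is yes, by a narrow route for the inefficacy rule and a wider one for prohibited medication.

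**3. Are such patients lost from the primary set?** The article gives no definition. The step from 64 to 60 counts dropouts as absent from the per-protocol set. The LOCF rule points the other way for any patient whom the definition keeps.

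**4. Illustration of the bias.** Let f be the excess number of Tr14 failures removed out of 64, each 30 mm worse than the Tr14 patients who stay. Both f and the 30 mm gap are assumptions. The true deficit is exactly 13 mm, so the nominal error is 2.5%.
- Shift in the difference = (f / 64) × 30 mm.
- Standard error = 25 × √(1/(64 − f) + 1/60).
- Error = Φ(−(1.96 − shift / standard error)).

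| f | Shift (mm) | Standard error (mm) | One-sided error |
|---|---|---|---|
| 1 | 0.47 | 4.51 | 3.2% |
| 2 | 0.94 | 4.53 | 4.0% |
| 3 | 1.41 | 4.55 | 4.9% |
| 4 | 1.88 | 4.56 | 6.1% |

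**5. Balanced removal.** In 40,000 simulated trials at a true 13 mm deficit, the four worst outcomes were removed from both arms. The mean difference stayed at 13.0 mm and the error was about 3.7%. The bias in the difference therefore needs an imbalance between the arms.

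**6. Power cost of requiring both sets.** With a true difference of 0, SD 25 mm, 64 per arm in the full analysis set and 4 random exclusions per arm, power is 83.1% in the full analysis set and 80.6% in the per-protocol set (exact t). By simulation, both succeed together in about 79% of trials.

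**The case against.** **What stands.** The withdrawal section gives reasons for leaving the study, not exclusions from an analysis set, and the set definition is something an article may leave to the full protocol. If a patient withdrawn after days 8 and 15 stays in the set, LOCF carries forward a value at least 30 mm above baseline, which counts against that patient's arm. Paracetamol rescue is permitted and physiotherapy rescue starts only on day 23, so neither is in itself a deviation before the endpoint. The exclusion counts and the 30 mm gap are not document figures. All of this limits what can be said about size.

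**Stronger readings that the article does not support.**
- *That treatment failures are certainly excluded, or the error is certainly inflated.* This depends on the unseen definition and on an imbalance that may not occur.
- *That the error reaches about 12%.* A simulation gives this figure if all 4 planned Tr14 losses are the worst Tr14 outcomes while dexamethasone loses 4 at random. That is an extreme case and nothing in the article points to it.
- *That the full analysis set is ignored.* Its analyses are planned, with estimates and 95% confidence intervals, so a conflict would be visible. The word exploratory does not demote it either, since the article applies that word to every analysis. What sets it apart is its supporting role.
- *That the sample size contains a slip because it allows only for dropout.* The article states its target in the per-protocol set and its allowance, and the arithmetic is right. A higher exclusion rate would be the reader's own assumption.
- *That the trial tests superiority to placebo on the wrong set.* No superiority hypothesis against placebo is stated; the comparisons are only listed.

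**What the objection does not answer.** The article still lets one post-randomization set settle the conclusion. Visibility of a conflict is not a rule for resolving it.

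**Conclusion.** The point holds as a weakness in the decision rule. Non-inferiority rests on the per-protocol set alone, outcome-related discontinuation can occur before day 22, and the sample size section treats dropouts as lost from that set. Unequal losses that fall more on Tr14 would favour non-inferiority.

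The size is illustrative: an error of about 3% to 6% instead of 2.5% for 1 to 4 excess Tr14 failures, assuming each is 30 mm worse, SD 25 mm and a true deficit of 13 mm. It shrinks if LOCF keeps failures in the set, and balanced removal leaves the difference unchanged. The label exploratory does not remove the problem, because the article fixes a test level and a margin and powers the trial for this test.

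**What to change.** State that non-inferiority is concluded only if the upper limit of the two-sided 95% confidence interval for Tr14 minus dexamethasone, in change of pain VAS at day 22, is below 13 mm in both the full analysis set and the per-protocol set. Make the full analysis set primary for the Tr14 versus placebo comparisons.

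Both analyses are already planned, so the change is one of wording and needs no more patients. The cost is a small loss of power: about 79% for joint success against about 80.5% for the per-protocol set alone, assuming 4 random exclusions per arm and an SD of 25 mm in both sets. As this falls just under the stated 80%, the plan should report the joint figure.

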**Table 3 Tab3:** **Statistical analyses to be performed**

ANCOVA with treatment group and center as qualitative factors and baseline value as covariate	Applicable for analyses at visits 5 and 7 for both treatment comparisons Tr14 injection solution against the comparators dexamethasone and placebo, respectively
	• Change from baseline in abduction-rotation pain VAS for active external rotation
	• Changes from baseline in ROM for abduction rotation as goniometry in degrees (active external, active internal, passive external, passive internal rotation)
	• Changes from baseline in ROM for hand-back range and hand-neck range as distance measurement in cm
	• Changes in DASH
Repeated measurements ANCOVA with treatment group, center, visit and treatment-by-visit interaction as qualitative factors and baseline value as covariate	Visits 5 and 7 included in analysis; both treatment comparisons Tr14 injection solution against the comparators dexamethasone and placebo, respectively:
	• Change from baseline in abduction-rotation pain VAS for active external rotation
Logistic regression model with treatment group, center and baseline value (positive/negative) as qualitative factors	Applicable for analyses at visits 5 and 7 for both treatment comparisons Tr14 injection solution against the comparators dexamethasone and placebo, respectively:
	• Jobe
	• Painful arc
Cochran-Mantel-Haenszel (CMH) test for ordered categorical responses stratified by center	Applicable for analyses at visits 5 and 7 for both treatment comparisons Tr14 injection solution against the comparators dexamethasone and placebo, respectively:
	• Patient’s global assessment
	• Investigator’s global assessment

ANCOVA = analysis of covariance; DASH = disability of arm, shoulder, hand; ROM = range of motion; Tr14 = Traumeel; VAS = visual analog scale.

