### Outcomes

The primary endpoint is change from baseline in abduction-rotation pain VAS (0–100 mm scale, 0 corresponds to no pain and 100 to extreme pain) at visit 5 (day 22) (Tr14 injection solution injections versus dexamethasone injections) for active external rotation. The abduction-rotation will be done with an internal rotation and external rotation and both actively and passively. However, the primary parameter is active rotation abduction with external rotation and only for this movement the VAS will be measured. During the shoulder examination, the active external abduction rotation must be the first movement during evaluation for pain VAS determination.

Secondary efficacy parameters include ROM, disability of arm, shoulder, hand (DASH) score and patient’s/investigator’s global assessment. For ROM the following movements will be analyzed [18,19]:Abduction rotation (active external, active internal, passive external, passive internal) measured by goniometry.Hand-back range and hand-neck range both measured in cm.Jobe (also known as ‘empty can’) test with measurement of pain and weakness (positive/negative). This will be examined as active movement.Painful arc after visit 4 (last injection) with measurement of pain (positive/negative). This will be examined as active movement.

Safety parameters include local tolerability, laboratory monitoring, vital signs and AEs. AEs will be standardized for terminology and classification, using Medical Dictionary for Regulatory Activities (MedDRA) (the latest available version will be used). Concomitant medications will be classified by site of action and therapeutic and clinical characteristics using the World Health Organization (WHO) DRUG dictionary (the latest available version will be used).

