## Discussion

The corticosteroids most commonly used in clinical trials for problems with the rotator cuff are methylprednisolone acetate and triamcinolone acetonide [8]. However, as crystalline corticosteroids, the appearance of these products in the vial is considerably different to Tr14 injection solution. Dexamethasone was chosen as the comparator corticosteroid as visually the solution is similar to Tr14 injection solution, thus aiding blinding of those administering the injections. The dose of dexamethasone was chosen to provide equivalence to 40 mg methylprednisolone acetate or 40 mg triamcinolone acetonide [20]. This dose of dexamethasone also provided a 2 ml injection, which was the same as the quantity of Tr14 injection solution to be used, again assisting blinding. A once-weekly dosing interval was chosen as an appropriate time interval to allow comparison with other injection therapies. A total of three injections was chosen as, in clinical practice, if there are no signs of improvement after 3 weeks of injections, it is unlikely that treatment would be continued.

To the best of our knowledge, dexamethasone has only been investigated in shoulder injuries on two previous occasions, first by Plafki *et al.* [21] using 4 mg dexamethasone-21-palmitat (equivalent to 2.5 mg dexamethasone) injected into the subacromial bursa once with ultrasound guidance for the treatment of subacromial impingement. This study was hindered by the need to stop the local anesthetic only arm of the study due to pain aggravation in some patients rendering the arm ethically unacceptable. However, results in both dexamethasone and triamcinolone acetate (10 mg) treatment groups were similar, suggesting that dexamethasone can provide similar results to triamcinolone acetate. The authors conclude that subacromial steroid injections could prevent the need for surgery in at least half of patients with chronic subacromial impingement syndrome.

The second study by Shibata *et al.* [22] was conducted in patients with full thickness rotator cuff tear, which was a specific exclusion criterion for our study, so the results, although positive, are not of relevance to our study population.

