The American Academy of Orthopaedic Surgeons (AAOS) guidelines on ‘Optimizing the Management of Rotator Cuff Problems’ state that they cannot recommend for or against the use of subacromial corticosteroid injections in the treatment of rotator-cuff-related symptoms in the absence of full thickness tear [27]. This is due to a lack of compelling evidence resulting in an unclear balance between benefits and potential harm. There is even less evidence about the efficacy of natural medications. It is hoped that the results of this trial will assist in providing more evidence to support physicians in their management of rotator cuff disease. Investigation of the efficacy and place in therapy of Tr14 injection solution is ongoing with further randomized-controlled trials underway.

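### Efficacy is concluded from non-inferiority to dexamethasone alone, while dexamethasone versus placebo is not planned and Tr14 versus placebo is not a condition of the conclusion

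*Protocol article*

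**What the plan says.** Under Statistical methods the efficacy criterion is "Clinical efficacy will be assessed as non-inferiority of Tr14 injection solution with respect to dexamethasone regarding the primary efficacy parameter", and the abstract says the same. The primary endpoint under Outcomes is tied to that pair: "at visit 5 (day 22) (Tr14 injection solution injections versus dexamethasone injections) for active external rotation". The test is "A one-sided test of non-inferiority of Tr14 injection solution with respect to dexamethasone at level 0.025". No second condition is attached.

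Table 3 lists four model types. The ANCOVA, logistic regression and Cochran-Mantel-Haenszel rows apply "for both treatment comparisons Tr14 injection solution against the comparators dexamethasone and placebo, respectively". The repeated-measures row reads "Visits 5 and 7 included in analysis; both treatment comparisons Tr14 injection solution against the comparators dexamethasone and placebo, respectively". No row contrasts dexamethasone with placebo.

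The sample size is "based on a non-inferiority margin of 13 mm and a standard deviation of 25 mm", with 60 evaluable patients per active arm. Randomization is 64, 64 and 32. Statistical methods also labels all analyses exploratory.

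On the strength of the control, the article points both ways. The Background cites meta-analyses in which subacromial corticosteroids did better than placebo. The Discussion says that "dexamethasone has only been investigated in shoulder injuries on two previous occasions", and it cites a guideline that recommends neither for nor against subacromial corticosteroids without a full-thickness tear, "due to a lack of compelling evidence resulting in an unclear balance between benefits and potential harm".

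**The concern.** Non-inferiority shows that a product works only if the control worked in the same trial, and by at least the margin. Otherwise being close to dexamethasone may mean only that both are close to saline. A three-arm trial can check this directly by comparing the active control with placebo. This trial pays for a placebo arm but does not plan that comparison.

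The other placebo comparison, Tr14 versus placebo, is planned but has no role in the conclusion. Followed as written, the plan allows efficacy to be concluded from the non-inferiority test while Tr14 shows no advantage over placebo, and it does not say how to read that outcome. Nothing in the article links the 13 mm margin to a dexamethasone effect, so the text offers no substitute for the check.

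**Working it through.** **Inputs.** From the sample size section: margin 13 mm, SD 25 mm, one-sided 0.025, 60 evaluable per active arm, dropout 6.25%, 32 randomized to placebo. Evaluable on placebo: 32 × (1 − 0.0625) = 30. The true dexamethasone effect over placebo, E, is not given and is varied from 0 to 20 mm. The SD of 25 mm is assumed to hold in all arms.

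**The plan's own figure.** SE = 25 × √(2/60) = 4.56 mm. At equal effects the noncentrality is 13/4.56 = 2.85. With 118 degrees of freedom (critical value 1.980) the power is 80.6%, so the stated 80% reproduces. 60/(1 − 0.0625) = 64 per active arm, and 64 + 64 + 32 = 160. The sample size arithmetic is sound.

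**Chance that an inert Tr14 is declared non-inferior.** If Tr14 equals saline, its true deficit against dexamethasone is E. The noncentrality becomes (13 − E)/4.56, and the probability is that of a noncentral t exceeding 1.980.

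| E (mm) | (13 − E)/4.56 | P(declared non-inferior) |
|---|---|---|
| 0 | 2.85 | 81% |
| 3 | 2.19 | 58% |
| 5 | 1.75 | 41% |
| 8 | 1.10 | 19% |
| 10 | 0.66 | 10% |
| 13 | 0 | 2.5% |
| 16 | −0.66 | 0.4% |
| 20 | −1.53 | 0.03% |

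So the nominal 2.5% protects against an inert product only if E is 13 mm or more.

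**What the placebo arm can show.** For 60 versus 30 patients, SE = 25 × √(1/60 + 1/30) = 5.59 mm. The 95% confidence interval has half-width 1.987 × 5.59 = 11.1 mm. Two-sided 5% power is 63% at 13 mm (13/5.59 = 2.33) and 81% at 16 mm (16/5.59 = 2.86).

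**Effect of adding a condition.** These figures come from a simulation with 60/60/30 patients, SD 25 mm, pooled variance on 147 degrees of freedom and no covariate adjustment. Better than placebo means that the 95% confidence interval excludes zero.

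| Inert Tr14, E (mm) | Non-inferiority alone | and Tr14 or dexamethasone better than placebo |
|---|---|---|
| 0 | 81% | 2.9% |
| 3 | 58% | 3.3% |
| 5 | 41% | 3.3% |
| 10 | 10% | 1.8% |

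| Both actives beat placebo by | Either/or rule | Tr14 must beat placebo | Dexamethasone must beat placebo |
|---|---|---|---|
| 13 mm | 60% | 56% | 48% |
| 16 mm | 72% | 69% | 63% |
| 20 mm | 79% | 78% | 75% |

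Non-inferiority alone passes in 81% of trials in all three rows of the last table.

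**The case against.** Five points can be made for the plan.

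- **The placebo arm is used.** A reader might infer that it is idle. It is not: every Table 3 row compares Tr14 with placebo, and estimates with 95% confidence intervals are promised. An inert Tr14 would beat placebo in only about 2.5% of trials, and that result would stand beside the non-inferiority result. If one three-arm ANCOVA is fitted, the dexamethasone-placebo point estimate is the difference of the two reported contrasts. This is a real partial safeguard. It does not supply the confidence interval for the control or a rule for reading discordant results.
- **Corticosteroids have support.** A reader might infer that the control probably does not work and that 81% is the expected error. The article does not support that. The Background reports a class benefit over placebo, the Discussion gives an equivalence rationale for the dose, and it describes an earlier study with results similar to triamcinolone. The guideline passage concerns an unclear balance of benefit and harm, not absence of effect. This stands, and it is why the table runs past 13 mm. Class evidence still does not show that this control worked in this trial.
- **The earlier dexamethasone studies.** It is tempting to say that neither gives a placebo-controlled effect. For the second study the article says only that the results were positive and the population different. Its control arm is not described, so the statement cannot be made from this document.
- **Everything is exploratory.** That lowers the stakes. The plan nevertheless sets a margin, a level and a power, and says that efficacy is judged by that test.
- **A separate analysis plan may add the contrast.** It may. But Table 3 sets out the analyses to be performed and limits each model to two named comparisons, and the efficacy criterion is stated here without a condition.

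**Conclusion.** The point holds as a gap in the stated contrasts and in the rule for interpretation. Non-inferiority alone carries the efficacy conclusion, the direct check of assay sensitivity is not planned, and the Tr14-placebo result does not condition the conclusion. An inert Tr14 passes in 81% of trials if dexamethasone has no effect and in 2.5% if its effect is 13 mm. Where the truth lies in that range is unknown from the document. The figures assume SD 25 mm in all arms, 60/60/30 evaluable patients and no gain from covariate adjustment.

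Severity: should fix. A reader might treat this as invalidating the trial. The exploratory label, the cited class benefit and the reported Tr14-placebo comparison do not support that.

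Nor does a dexamethasone-placebo interval that excludes zero show that the effect exceeds 13 mm. With a half-width of about 11 mm, the comparison with the margin can only be descriptive.

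**What to change.** 1. Add dexamethasone versus placebo at visits 5 and 7 to Table 3, from the same ANCOVA, with estimate and 95% confidence interval. Show it beside the 13 mm margin as a descriptive comparison.
2. State in Statistical methods that day 22 non-inferiority is read as evidence of efficacy only if Tr14 or dexamethasone is better than placebo (95% confidence interval excluding zero). Otherwise report assay sensitivity as not shown and the non-inferiority result as inconclusive for efficacy.

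This needs wording only, with no added patients or visits. The either/or rule limits the false claim for an inert Tr14 to about 3.3%.

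The price is a harder claim. If both actives beat placebo by 13, 16 or 20 mm, the chance of the efficacy reading falls from 81% to about 60%, 72% or 79%. Requiring Tr14 itself to beat placebo gives 56%, 69% or 78%. At a true 13 mm effect, each placebo contrast taken alone misses in about 37% of trials (100% − 63%), so a failed check should be reported as inconclusive and not as proof that the control failed.

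### The repeated-measurements ANCOVA in Table 3 fits one baseline slope to Day 22 and Week 15; if the true slopes differ, its visit-specific contrasts and its treatment-by-visit interaction carry part of any chance baseline imbalance (minor)

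*Protocol article*

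**What the plan says.** The Statistical methods section of the protocol article makes the primary analysis "A one-sided test of non-inferiority of Tr14 injection solution with respect to dexamethasone at level 0.025", from an ANCOVA of the change in pain VAS at Day 22 with treatment, center and baseline VAS.

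Table 3 then analyzes that VAS change in two ways, for Tr14 against dexamethasone and against placebo:

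- First row: "ANCOVA with treatment group and center as qualitative factors and baseline value as covariate", applied at Visit 5 and at Visit 7. Each fit has its own baseline slope and its own center effects.
- Second row: "Repeated measurements ANCOVA with treatment group, center, visit and treatment-by-visit interaction as qualitative factors and baseline value as covariate", with "Visits 5 and 7 included in analysis". Only treatment is crossed with visit. Baseline and center enter as main effects, so one baseline slope and one set of center effects serve both visits.

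The Statistical methods section also says that reported estimates and confidence intervals come from the models in Table 3, that missing efficacy values are filled by LOCF, and that all analyses are exploratory.

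**The concern.** Visit 5 is one week after the last injection; Visit 7 is at Week 15. The Concomitant care section allows physiotherapy only from Day 23. Baseline pain could therefore predict the two outcomes with different strength. If it does, a shared slope lies away from the true slope at one visit or at both, and an arm that starts with more pain by chance is adjusted too much or too little.

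What is at stake is the quality of an additional analysis: its visit-specific contrasts and, above all, its comparison of the treatment effect between visits, which the separate ANCOVAs do not provide.

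**Working it through.** **The plan's own figure.** The Sample size calculation section uses a "non-inferiority margin of 13 mm and a standard deviation of 25 mm for the response variables". The normal approximation gives 2 × 25² × (1.960 + 0.842)² / 13² = 58.1, so 59 per arm. The t-test gives power 0.7998 at 59 and 0.8065 at 60. The stated 60 is reproduced, as are 60 / (1 − 0.0625) = 64 and 64 + 64 + 32 = 160. Nothing below changes this.

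**Assumed inputs.** The article gives no baseline SD, baseline slopes or within-patient correlation. Assumed here: baseline SD 20 mm (range 10 to 25), slopes of the change score −0.4 at Day 22 and −0.8 at Week 15 (equivalently 0.6 and 0.2 for the VAS itself), complete data and 10 centers. Of these, only the 10 centers are stated in the article.

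**Error per mm of imbalance.** At visit v the treatment estimate is off by about (b_v − b_common) × (baseline difference between arms). With an unstructured covariance, b_common = w·b_22 + (1 − w)·b_15, where w = (s_15² − ρ·s_22·s_15) / (s_22² + s_15² − 2ρ·s_22·s_15).

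| Residual SDs (mm), ρ | w | b_common | Day 22 error | Week 15 error | Simulated |
|---|---|---|---|---|---|
| 25 and 25, 0.5 | 0.500 | −0.60 | +0.20 | −0.20 | +0.21, −0.17 |
| 20 and 30, 0.5 | 600/700 = 0.857 | −0.46 | +0.06 | −0.34 | +0.04, −0.35 |
| 20 and 30, 0.7 | 480/460 = 1.043 | −0.38 | −0.02 | −0.42 | 0.00, −0.39 |

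The last column is from 3,000 simulated trials per scenario at 60 v 60. With visit-specific slopes, the dependence on imbalance stayed within 0.04 of zero.

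**In mm.** The SE of the baseline difference is 20 × √(2/60) = 3.65 mm, so a two-SE imbalance is 7.3 mm.

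- Equal residual SDs: 0.2 × 7.3 = 1.5 mm at each visit, in opposite directions.
- Residual SDs 20 and 30: 0.35 × 7.3 = 2.6 mm to 0.39 × 7.3 = 2.8 mm at Week 15, where the SE of the treatment difference is about 30 × √(2/60) = 5.5 mm. Almost nothing remains at Day 22.
- Over baseline SDs of 10 to 25 mm and slope gaps of 0.1 to 0.4, with the common slope midway, the Day 22 shift is 0.09 to 0.91 mm at one SE and 0.18 to 1.79 mm at 1.96 SE.
- Placebo contrast: 32 × (1 − 0.0625) = 30 patients, so the SE of the imbalance is 20 × √(1/60 + 1/30) = 4.5 mm.

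**Treatment-by-visit interaction.** Its error is (b_22 − b_common) − (b_15 − b_common) = b_22 − b_15 = 0.4 per mm, wherever the common slope falls. At one SE of imbalance this is 0.4 × 3.65 = 1.5 mm. With SDs 25 and 25 and ρ 0.5, the within-patient difference has SD √(625 + 625 − 625) = 25, so the interaction has an SE of 25 × √(2/60) = 4.6 mm.

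**Precision.** In a simulation with outcome SD 25 and slopes 0.6 and 0.2, adding baseline-by-visit cut the SD of the contrast from 4.055 to 4.018 at Visit 5 and from 4.495 to 4.426 at Visit 7, which is 2% and 3% of variance.

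**Agreement with the primary ANCOVA.** Mean absolute gap at Day 22 (1,500 trials, 60/60/30, SDs 25 and 25, ρ 0.5):

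| Model | Slopes 0.4 apart | Equal slopes |
|---|---|---|
| As written | 0.71 mm | 0.46 mm |
| + baseline-by-visit | 0.44 mm | 0.445 mm |
| + baseline-by-visit and center-by-visit | 0.000 mm | 0.000 mm |

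**Average bias.** Over the simulated scenarios the mean Day 22 error of the model as written ran from −0.21 to 0.11 mm (Monte Carlo SE 0.10 to 0.12), so no material bias.

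**The case against.** The strongest case against has four parts.

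- **The defect is conditional.** With equal slopes there is no mis-adjustment, and nothing in the article shows that the slopes differ. This stands. A reader might infer that the common slope is wrong at both visits; the documents do not support that, and in the scenarios with SDs of 20 and 30 mm the Day 22 error is close to zero even with slopes 0.4 apart.
- **No main conclusion depends on it.** The non-inferiority test is the single-visit ANCOVA, separate ANCOVAs are planned at both visits for both comparators, and everything is labelled exploratory. The support that the article names for the primary result is the full analysis set, not this model. All of this stands and limits the point to a minor one.
- **With baseline and center both crossed with visit, the row repeats the separate ANCOVAs.** This is true of the visit-specific contrasts when the data are complete, as LOCF makes them in effect. What the row still adds is the treatment-by-visit interaction, and that is where the common slope passes on the whole slope gap.
- **An article may leave parameterization to a fuller document.** That fuller document may already contain the term. But Table 3 lists this model term by term, includes one interaction with visit and is named as the source of the reported estimates. It is therefore fair to ask that the list be completed.

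A reader might also blame any difference between the two planned Day 22 estimates on the baseline slope alone. That is not so: with equal slopes the mean gap is still 0.46 mm, because center effects are shared across visits.

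**Conclusion.** The point holds as a minor, conditional one. As listed, the model fits one baseline slope to two visits. If the slopes differ by 0.4, the error in the trial actually run is about 0.2 mm per mm of baseline imbalance at each visit with equal residual SDs. With SDs of 20 and 30 mm it is near zero at Day 22 and up to about 0.4 at Week 15. The slopes, baseline SD and correlation behind these figures are assumptions, and smaller slope gaps shrink the error in proportion.

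Two stronger readings should be resisted. The error is not a systematic bias for or against Tr14: it depends on the imbalance that happens to arise and averages out over randomization. Nor should the Week 15 error be set against the 13 mm margin, which belongs to the primary variable at Day 22. The primary test and the sample size are untouched.

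**What to change.** In the second row of Table 3, and in the full analysis plan if it is not already there, add a baseline-by-visit interaction to the repeated-measurements ANCOVA. With two visits this costs one degree of freedom. In the equal-slopes simulation the model SE at Day 22 was 4.70 mm with and without the term, so where the term is not needed it corrects nothing and costs practically nothing.

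State also whether center is crossed with visit. If the model's Day 22 estimate is meant to match the primary ANCOVA, center-by-visit is needed too: nine further degrees of freedom with 10 centers (10 − 1 = 9). If not, say that small differences between the two estimates are expected and that the single-visit ANCOVA is the one that counts. No change to data collection, sample size or the primary analysis follows.
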